# Efficacy of a smartphone application for helping individuals with type 2 diabetes mellitus manage their blood glucose: a protocol for factorial design trial

**DOI:** 10.1186/s13063-023-07489-5

**Published:** 2023-07-22

**Keywords:** Type 2 diabetes mellitus, Diabetes app, Factorial design trial, Chinese, Blood glucose management, Blood glucose monitoring

## Abstract

**Background:**

China has the largest number of individuals with type 2 diabetes mellitus (T2DM) in the world, and most lack knowledge about glycemic control and health management. This trial will examine whether a smartphone application can improve blood glucose management among individuals with T2DM.

**Methods:**

This will be a 2-center, factorial design, equal proportional distribution, superiority trial conducted in outpatient endocrinology clinics at two tertiary hospitals in Chengdu, China. The trial will enroll smartphone-literature individuals at least 18 years old who have been diagnosed with T2DM based on glycosylated hemoglobin (HbA_1c_) of at least 7.0%. Individuals will be randomly assigned to receive routine care with standard education about T2DM and glycemic control (Control), routine care as well as weekly telephone reminders to self-monitor blood glucose (Reminder), routine care and a smartphone application providing information about glycemic control and health management with T2DM (App), or the combination of routine care, the smartphone application, and weekly telephone reminders (App + Reminder). After 6 months of these interventions, participants will be analyzed for the primary outcome of HbA_1c_ as well as the secondary outcomes of blood glucose monitoring frequency, body mass index, blood pressure, knowledge about diabetes, health beliefs related to diabetes, diabetes self-management behavior, and satisfaction with the smartphone application.

**Discussion:**

This trial will determine whether a smartphone application can improve glycemic management among Chinese with T2DM. The findings may help guide the development of effective applications in China and elsewhere.

**Trial registration:**

Registration in the Chinese Clinical Trial Registry (ChiCTR) under registration number ChiCTR2100042297: 
https://www.chictr.org.cn/bin/userProject. 17 January 2021.

**Supplementary Information:**

The online version contains supplementary material available at 10.1186/s13063-023-07489-5.

## Introduction

### Background and rationale {6a}

In 2021, approximately 537 million people at 20–79 years old had diabetes, according to the International Diabetes Federation [1]. China contains the largest proportion of these individuals, most of whom have type 2 diabetes mellitus (T2DM) [1]. People with T2DM should self-monitor blood glucose levels in order to adjust their lifestyle and diet as needed to ensure good glycemic control. However, many individuals with T2DM do not monitor themselves [2, 3].

The ubiquity of smartphones and smartphone-based applications (“apps”) provides an excellent opportunity for educating individuals with T2DM about their condition and promoting self-monitoring of blood glucose. Current estimation suggests that there are nearly 1700 smartphone applications related to diabetes [4]. Studies so far have suggested that such applications can help people manage the disease [5] as well as reduce body weight [6] and blood glucose level [7].

However, a survey of 30 provinces in China in 2019 showed that only about 10% of individuals with T2DM used applications related to diabetes [8]. The frequency of using such applications was particularly low in Sichuan Province, which may reflect that its per capita gross domestic product (GDP) is substantially lower than that of the 10 Chinese provinces with highest per capita GDP [8].

A survey of more than 1276 individuals with T2DM identified “Dnurse” (dnurse.com/v2/app) as the most popular diabetes-related smartphone application in China [8]. The present trial will assess whether Dnurse can help individuals with T2DM manage their glucose levels and, more generally, their disease condition. It will also assess users’ satisfaction with the application.

### Objectives {7}

The aims of the study are to:

Evaluate the effect of the smartphone application Dnurse on glycemic management and disease control in individuals with T2DMAssess whether the application influences compliance with blood glucose monitoringMeasure user satisfaction with the application

### Study design {8}

This will be a 2-center, factorial design, equal proportional distribution, superiority trial conducted in outpatient endocrinology clinics at two tertiary hospitals in Chengdu, China, which will be conducted from 2021 to 2023. 

In reporting the protocol for this study, we followed the SPIRIT 2013 checklist. Individuals will be randomly allocated to the Control group, Reminder group, App group, and App + Reminder group. Flow diagram of the study is shown in Fig. 1.

**Fig. 1 Fig1:**
[figure not shown]
Flow diagram of the study. The questionnaires ① to ⑤ include the general situation questionnaire, Diabetes Knowledge Scale, Health Belief Questionnaire, Type 2 Diabetes Self-management Behavior Scale and User satisfaction with Dnurse application and its paired glucose meter

## Methods: participants, interventions, and outcomes

### Study setting {9}

Since October 2021, the trial has been underway at two tertiary general hospitals (“grade A” in the Chinese hospital classification scheme) in Chengdu, China. At each site, two researchers have been designated to carry out the trial. A SPIRIT schedule of procedures and events is demonstrated in Table 1.

**Table 1 Tab1:** Schedule of procedures and assess

**TIMEPOINT**		**STUDY PERIOD**		
	**Enrolement**	**Baseline**	**Intervention**	**Endpoint**
	**-**	**0 months**	**3 months**	**6 months**
**Enrolement:**				
Eligibility screen	**X**			
Informed consent	**X**			
Allocation	**X**			
**Interventions:**				
Control group		**X**	**X**	
Reminder group		**X**	**X**	
App group		**X**	**X**	
App + Reminder group		**X**	**X**	
**Assessments:**				
chronic complications related to diabete		**X**		**X**
acute complications related to diabetes		**X**		**X**
diabetes treatments		**X**		**X**
DKN, HBQ, 2-DSCS		**X**		**X**
satisfaction with the smartphone application				**X**
height, weight, blood pressure and HbA_1c_		**X**	**X**	**X**
frequency of blood glucose monitoring			**X**	**X**

Chronic complications related to diabetes: hypertension, cardiovascular disease, cerebrovascular disease, peripheral vascular disease, kidney disease, peripheral neuropathy, eye disease and diabetic foot; acute complications related to diabetes: hypoglycemia and lactic acidosis or ketoacidosis; diabetes treatments: non-drug therapy, oral hypoglycemic drugs, and insulin therapy

*DKN* Diabetes Knowledge Scale, *HBQ* Health Belief Questionnaire, *2-DSCS* Type 2 Diabetes Self-management Behavior Scale, *user satisfaction with Dnurse application*, custom-made questionnaire to assess user satisfaction with Dnurse application, HbA_1c_ Glycosylated hemoglobin

### Eligibility criteria {10}

Inclusion criteria are as follows:

Persons who are diagnosed with T2DM based on the criteria of the World Health Organization and diagnosed by a secondary or higher hospitalPersons glycosylated hemoglobin (HbA_1c_) ≥ 7.0%Persons at least with a primary school educationPersons aged at least 18 years oldPersons with smartphone literacy. Smartphone literacy is assessed by asking potential participants whether more than three commonly used applications are installed on their smartphonesPersons who have residence in Chengdu for at least the previous 12 monthsPersons who have willingness to participate and provide informed consent

Exclusion criteria include:

Persons with a previous diabetes-related application experiencePersons with a history of mental illness, cognitive impairment, or communication disorder, based on self-reportPersons with pregnancy or planning to become pregnantPersons with any severe diseases posing threat to lifePersons with current diabetes-related hospitalization

### Who will take informed consent? {26a}

Written informed consent will be obtained from participants with type 2 diabetes participating in this study. Informed consent forms will be given to each potential participant, which they can read with their relatives and friends, and explanations will be given to help them make a decision. Participation in the study is completely voluntary, and participants can refuse to be in the study or withdraw from the study at any time without discrimination, medical treatment, and benefits will not be affected.

### Additional consent provisions for collection and use of participant data and biological specimens {26b}

The use of participants’ data and the collection of blood samples have been stated in the informed consent form, which have also been included in the ethics declaration.

## Interventions

### Intervention description {11a}

The Control group will undergo routine diabetes management: they will receive a standard portable glucose meter (Dnurse He pro wisdom; Beijing Dnurse Technology Ltd, Beijing, China) and blood glucose monitoring record book. The recommended timing and frequency of blood glucose monitoring will be explained to them according to national guidelines [9].

The Reminder group will receive the same materials as the Control group as well as a weekly telephone reminder to self-monitor blood glucose regularly. These reminders will be given by specially selected nursing undergraduates who have been trained in the rationale, interventions, and objectives of the study. Only nursing students who performed well on post-training testing are allowed to participate in the study. During the telephone call, students will ask participants whether they are self-monitoring regularly and, if not, what are the reasons.

The App group will receive a smart blood glucose meter (Dnurse SPUG mobile blood glucose uric acid tester; Beijing Dnurse Technology Ltd), and they will be led by a specially trainer researcher to download the Dnurse App 4.0.16 (dnurse.com/v2/app), designed to work smoothly with the smart blood glucose meter. The researcher will show the study participants how to open a personal account on the application and how to generate personalized diet and exercise programs, glucose control targets, and a blood glucose monitoring plan; how to access the food bank, disease information, and real-time blood glucose analysis and recommendations within the application; and how to set reminders to take medication and engage in other behaviors.

The App + Reminder group will receive the same materials and training as the App group, together with weekly telephone reminders like the Reminder group.

If members of the Control group and the Reminder group experience acute complications of diabetes, such as excessively high or low blood glucose, trial investigators will advise them to seek medical treatment as per standard procedures. If members of the App group and the App + Reminder group trigger a “critical value” alarm on the application, the customer service staff of the application’s manufacturer will call them by telephone and provide advice or information as per standard procedures. Both devices pass through ISO13485 and EU CE certifications.

### Criteria for discontinuing or modifying allocated interventions {11b}

Possible reasons for subject’s voluntary withdrawal are as follows: subjects found to be pregnant and subjects lost to follow-up.

### Plans to promote participant retention and complete follow-up {11c}

To promote participants’ participation in the trial, blood glucose test strips will be given to participants free of charge during the trial.

### Relevant concomitant care permitted or prohibited during the trial {11d}

Participants are allowed to go to the doctor or stay in the hospital normally during the trial, and the drug type and dose will be adjusted. If participants become pregnant during the trial, they will withdraw from the study.

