### Adverse event reporting and harms {22}

The adverse events in this study refer to hypoglycemia and will be registered at 3rd month and 6th month after the intervention. And the participants inform the doctor of the number of hypoglycemia times during outpatient visits.

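### The protocol's definitions disagree on whether very high glucose is a recorded event, and hospital stays have no data item, so these harms may not be counted by arm

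*Protocol article*

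**What the plan says.** Five places in the protocol article bear on this point.

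- **{11d}, concomitant care.** Stays are permitted: "Participants are allowed to go to the doctor or stay in the hospital normally during the trial". Treatment may change as well: "the drug type and dose will be adjusted".
- **{11a}, intervention description.** If Control or Reminder participants "experience acute complications of diabetes, such as excessively high or low blood glucose, trial investigators will advise them to seek medical treatment". If App or App + Reminder participants trigger a critical-value alarm, "the customer service staff of the application’s manufacturer will call them by telephone and provide advice or information".
- **Table 1 and its footnote.** Acute complications are marked at baseline and month 6 and defined as "acute complications related to diabetes: hypoglycemia and lactic acidosis or ketoacidosis". Diabetes treatments, in three broad classes, are marked at the same two times.
- **{18a}, outcome collection.** Any acute or chronic complication arising on study is recorded at month 6. The acute complications named are those in the Table 1 footnote, but they are introduced as examples. Treatments are mentioned at baseline only.
- **{22}, harms.** "The adverse events in this study refer to hypoglycemia and will be registered at 3rd month and 6th month after the intervention".

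**The concern.** Section {11a} shows that the investigators expect some participants to reach glucose values serious enough to need medical contact, and it counts high values as well as low ones. Yet the section that defines adverse events and the table that sets the schedule both leave high values out unless they reach ketoacidosis. Staff who follow Table 1 and {22} would have no reason to record them.

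The app under test generates glucose targets and gives real-time recommendations, so acute high-glucose events and admissions are a natural part of a harms comparison. The trial is open label apart from the HbA1c testers ({17a}, {17b}) and has no data monitoring committee ({21a}). Section {21b} nevertheless allows the trial to stop if one treatment is clearly better. If these events are not collected in the same way in every arm, they can neither be reported nor inform that decision. An analysis plan cannot repair this later, because it cannot tabulate what was not collected.

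**Working it through.** The plan states no figure on this point, so there is nothing to reproduce. The check sets the sections side by side.

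**Step 1. What each place counts**

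| Event on study | {11a} | Table 1 footnote | {18a} | {22} |
|---|---|---|---|---|
| Hypoglycemia | Acute complication | Listed | Listed, month 6 | Adverse event, months 3 and 6 |
| Ketoacidosis or lactic acidosis | Not named | Listed | Listed, month 6 | Outside the definition |
| High glucose without ketoacidosis | Acute complication | Not listed | Covered only if the list is read as open | Outside the definition |
| Hospital stay (permitted by {11d}) | Not named | Not listed | Not listed | Outside the definition |

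The third row is an inconsistency. {11a} speaks of "acute complications of diabetes, such as excessively high or low blood glucose", the footnote gives a list with no indication that it is open, and {22} is narrower still: "The adverse events in this study refer to hypoglycemia". The fourth row is a gap: the event is foreseen, but no item is named for it.

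**Step 2. Follow typical events through the sections**

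- *Control participant, very high glucose without ketoacidosis, referred between visits.* An acute complication under {11a}, not one under the Table 1 footnote, and not an adverse event under {22}. Under {18a} it depends on who reads the list. If only the dose changes, the treatment class in Table 1 does not change either.
- *App participant, same event.* The alarm leads to a call from the manufacturer's staff. No entry of that call in the trial data is stated.
- *Any participant admitted with ketoacidosis.* The ketoacidosis is recorded at month 6. The stay, its date and its reason have no named item.

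**Step 3. Compare the routes by arm**

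In the two no-App arms the event is described as reaching the trial investigators. In the two App arms it is described as reaching the manufacturer. If recording depends on what investigators happen to learn, the App and no-App counts come from different processes, even for identical events.

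**Step 4. Compare the timing**

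Hypoglycemia is registered at months 3 and 6 under {22}, but the acute-complication item that contains it is marked only at baseline and month 6 in Table 1, with on-study events at month 6 in {18a}. Treatments are marked at month 6 in Table 1 but mentioned only at baseline in {18a}. These differences also need reconciling.

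**Step 5. What remains visible by arm**

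Hypoglycemia (months 3 and 6); ketoacidosis, lactic acidosis and new chronic complications, including cardiovascular, cerebrovascular and kidney disease and diabetic foot (month 6); a change of treatment class (month 6, per Table 1); and HbA1c (months 3 and 6). What may be lost is acute high glucose short of ketoacidosis, the medical contacts it leads to, and hospital stays as such.

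**The case against.** The case on the other side has real force.

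- **The open list may suffice.** {18a} records any acute complication at month 6, and {11a} calls very high glucose an acute complication. Read together, the event is recorded. This reading is possible, but the Table 1 footnote and {22} point the other way and nothing says which prevails. What stands is that one cannot claim these events are recorded nowhere.
- **The article is a condensation.** The full protocol is available on request ({31c}), and the date and reason of a stay are ordinary case-report-form detail. That stands for the detail. It does not remove the explicit hypoglycemia-only definition in {22} or the disagreement between published definitions.
- **Sustained loss of control is the primary outcome.** HbA1c is measured at months 3 and 6 by blinded testers, so a lasting deterioration would be seen. That stands. Acute events and admissions are a separate question.
- **Entry criteria.** A reader might see a contradiction between excluding people currently in hospital for diabetes ({10}) and permitting stays later ({11d}). There is none: one governs entry, the other ordinary care afterwards.

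A stronger inference is tempting: that unrecorded stays act as a co-intervention and bias the HbA1c result. The documents do not support it. Stays occur after randomisation. If the App changes admissions, the consequence for HbA1c is part of the effect estimated under the planned intention-to-treat analysis ({20c}). If an imbalance arises by chance, the standard error already allows for it. Nor can a size be put on it: the documents give no admission rate and no HbA1c change per stay, and convenient assumptions easily conflict. For example, if 3% of 264 had a stay, that is about 8 people. Even with all 8 on one side of the App/no-App split, the imbalance is 8/132 = 6.1 percentage points, so one of 10 points could not occur.

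**Conclusion.** The point holds as a matter of harms recording. {11a}, Table 1, {18a} and {22} do not agree on whether very high glucose is a recorded event, and hospital stays are foreseen in {11d} without being listed for collection. Followed as written, the harms comparison may miss both, and the route by which they come to notice differs between App and no-App arms.

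The conclusion assumes that site staff work from Table 1 and {22} as published. If a case report form already asks about these events in every arm, what remains is to bring the published definitions into line.

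No numerical size is claimed. Any counts are likely to be small and should be read descriptively. As an illustration with assumed counts, 4 against 11 stays among 132 per side (264/2) is 3.0% against 8.3% and gives a two-sided Fisher p of 0.11, which is worth reporting but not conclusive.

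A reader might infer that serious events in general are invisible, or that the primary analysis is compromised. Neither follows: several serious complications and treatment class are recorded at month 6, and the HbA1c comparison stands. This is a cheap improvement, not a flaw that threatens the trial's main result.

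**What to change.** 1. Reconcile {11a}, the Table 1 footnote, {18a} and {22} so that they state in the same terms whether high glucose without ketoacidosis is a recorded event. Align the recording times of acute complications, and the month 6 entry for treatments, between Table 1 and the text.
2. Extend the adverse-event definition in {22} and the Table 1 row to cover diabetes-related hospital stays and high-glucose events that led to medical contact, whether an investigator referral or a manufacturer alarm call. Both routes must count, otherwise the App and no-App arms are compared on different processes.
3. Ask about these events in identical words in all four arms at months 3 and 6, with date and reason.
4. Report the counts by arm descriptively.

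Leave the intention-to-treat HbA1c analysis as it is. Do not add a sensitivity analysis that flags participants by hospital stay: a stay happens after randomisation and may depend on the arm, so conditioning on it can itself introduce bias.

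The cost is a few questions at visits already scheduled, one table row and a short amendment through the route in {25}. Visits become slightly longer, and events before the amendment would have to come from recall or hospital records. This changes only what is recorded, not any treatment, alarm or referral rule.

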### Provisions for post-trial care {30}

For the two groups that do not use the APP, we will introduce the relevant information of the Dnurse APP to them after the trial, and they will choose whether to use the APP for diabetes management according to their wishes.

### Outcomes {12}

Data are collected at three times, including two follow-up visits at baseline, the 3rd month after intervention, and the 6th month after intervention, through participant visits to the hospital by the investigator.

The primary outcome is the level of HbA_1c_, which reflects blood glucose levels over the preceding 2–3 months and is a good indicator of blood glucose control [10, 11]. All results will be made by high-performance liquid chromatography at the same certified external laboratory to ensure consistency.

Secondary outcomes include frequency of blood glucose monitoring, body mass index, blood pressure, knowledge about diabetes, health beliefs related to diabetes, and diabetes self-management behavior. The App and the App + Reminder groups will also be asked about their satisfaction with the smartphone application.

The following questionnaires will be used for the study:

Change in knowledge from baseline as measured by the Chinese version of the Diabetes Knowledge Questionnaire (DKN) [12]. Each item is scored from 0 to 1, and the total scores range from 0 to 23 (Higher score indicating greater knowledge of diabetes)Change in health belief from baseline as measured by the Health Belief Questionnaire (HBQ) [13]. Scores ranging between 20 to 100 (higher score indicating better outcomes)Change in self-management behavior from baseline as measured by the Type 2 Diabetes Self-management Behavior Scale (2-DSCS) [14]. Total scores range from 26 to 130 (higher score indicating better outcomes)Custom-made questionnaire to assess user satisfaction with Dnurse application and its paired glucose meter. Participants who use the APP 6 months after the intervention will complete the assessment. The 5-level Likert scoring method is adopted, and the total scores range from 11 to 55 points (Table 2)

**Table 2 Tab2:** Custom-made questionnaire to assess user satisfaction with Dnurse application

Item	Very satisfied	Satisfied	Neither satisfied nor dissatisfied	Slightly dissatisfied	Very dissatisfied
1. Your satisfaction with the application interface					
2. Your satisfaction with the application’s ease of use					
3. Your satisfaction with how the application records blood glucose					
4. Your satisfaction with the health information provided by the application					
5. Your satisfaction with using the application to manage diabetes					
6. Your satisfaction with the application’s safety					
7. Your satisfaction with the application’s performance (accuracy of results, speed of responses)					
8. Your overall satisfaction with the application					
9. Your satisfaction with the ease of operation of the glucose meter					
10. Your satisfaction with the stability of the connection between the glucose meter and application					
11. Your overall satisfaction with the glucose meter					

Instructions: Please choose the one response with which you agree most

